### Outcomes

Efficacy of the interventions will be determined by comparing change scores (baseline to post treatment) on a variety of standardized outcome measures taken at baseline, post-treatment and 8 weeks post-intervention. The primary outcome measure is comfortable gait speed as measured by the five-metre walk test [54]. Following stroke, gait speed is frequently reduced compared to age matched normals [5,55,56]. Gait speed has been shown to be reliable (r = 0.94)[57], responsive to change (SRM = 1.22; effect size = 0.83) [54], and significantly related to independent community ambulation [11].

Secondary outcome assessment will include measures of maximal gait speed, walking endurance (Six Minute Walk Test), dynamic balance (Functional Balance Test) [58], balance and walking related self-efficacy (Activities- specific Balance Confidence Scale) [59], walking function (modified Functional Ambulation Categories) [60], walking participation (5-day daily step activity - StepWatch 3 step activity monitor) [61,62], community reintegration (Life Space Questionnaire) [63,64], health related quality of life (Stroke Impact Scale 3.0) [65], goal attainment (Patient Specific Functional Scale) [66] and mean number of trainers per training session.

In addition, the baseline assessment will include the collection of demographic information, assessment of cognitive function (Mini Mental Status Exam) [36], presence of depression (Geriatric Depression Scale -15) [67], and the Chedoke-McMaster Stroke Assessment Leg and Foot stages of motor recovery [68]. At follow-up, information will be collected regarding participation in physiotherapy and any change in health status. This information will be used to describe the groups and interpret the results of the interventions.

Training and assessor therapists will record any of the following adverse events that occur during or between sessions: 1) falls (unintentionally landing on the ground), 2) any injury during session, 3) myocardial infarction (confirmed by physician and/or health records), 4) new stroke or transient ischemic attack (confirmed by physician and/or health records), 5) hospitalization for any cause, 6) death of any cause.

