### Statistical Analysis

The trial results will be reported in accordance with the CONSORT criteria [http://www.consort-statement.org]. The flow of patients in the trial will be summarized using a flow-diagram. The baseline characteristics and outcomes scores of the patients will be analyzed using descriptive statistics reported by group as mean (standard deviation [SD]) or median (first quartile [Q1], third quartile [Q3]) for continuous variables depending on the distribution and count (percent) for categorical variables. Intention to treat analysis technique will be used for the primary analysis [71]. Missing data will be handled through multiple imputation technique [72]. All statistical tests will be performed using two-sided tests at the 0.05 level of significance. The Tukey's HSD method will be used to adjust the level of significance for testing for secondary outcomes. For all models, the results will be expressed as estimate of mean difference (or odds ratios for binary outcomes), standard errors, corresponding two-sided 95% confidence intervals and associated p-values. P-values will be reported to three decimal places with values less than 0.001 reported as < 0.001. Adjusted analyses will be performed using regression techniques to investigate the residual impact of key baseline characteristics on the outcomes (i.e. age, time since stroke onset, comfortable gait speed, and training site). Goodness-of-fit will be assessed by examining the residuals for model assumptions and chi-squared test of goodness-of-fit. All analyses will be performed using SPSS version 16.0 for Windows or SAS 9.2 (Cary, NC).

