#### Secondary Analysis

Mixed design analysis of variance will be used to compare the two groups' baseline, post-intervention and follow-up scores on all other secondary measures. The two factors will be time and group. Descriptive statistics (i.e. means, or frequencies) will be used to present data related to adverse and serious adverse events by groups. Any apparently significant differences between groups will be analysed for significance using chi square statistics. In an effort to describe the two interventions, the mean number of steps taken per session will be counted in a convenient sub-sample of participants using the step activity monitors. Independent samples t-test statistic will be used to compare the mean number of steps taken per session by the two groups during treatment sessions.

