#### Sensitivity Analyses

Sensitivity analyses will be performed to assess the robustness of the results. First, there is likely to be high inter-correlations among all outcomes. We will use multivariate analysis of variance (MANOVA) approach to analyze all outcomes simultaneously. This method accounts for possible correlations among all outcomes and provides for a global assessment of differences between groups with an indication of where differences exist. Second, we will use generalized estimating equations (GEE) [73] to account for possible serial correlation of measurements within a patient overtime. Unlike ordinary linear regression, GEE allows accounting possible correlation of outcome scores for the same patient over time. We will use sensitivity analysis to explore potential clustering of measurements/outcomes from the same patient. The clustering effect, measured by intra-class correlation coefficient, will be assumed to be equal across patients. Sensitivity analysis will also include a between-group comparison of post-intervention comfortable gait speed in participants who completed at least 12 of the 15 training sessions using analysis of variance. Refer to Table 3 for a summary of the planned analyses.

**Table 3 T3:** Summary of planned primary, secondary and sensitivity analyses

*Objective/Variable*	*Hypothesis*	*Outcome measure (type)* *[continuous (c), binary (b)]*	*Method of Analysis*

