**2) Secondary (T2, T3)**			
Secondary outcomes			
a) Fast walking speed	MLWP > BWSTT	Fast Gait Speed (c)	ANCOVA
b) Walking endurance	MLWP > BWSTT	Six minute walk test(c)	ANCOVA
c) Balance and walking related self-efficacy	MLWP > BWSTT	Activities-specific Balance Confidence Scale (c)	ANCOVA
d) Dynamic balance	MLWP > BWSTT	Functional Balance Test(c)	ANCOVA
e) Mobility participation	MLWP > BWSTT	Life Space Questionnaire (c)	ANCOVA
f) Health-related quality of life	MLWP > BWSTT	Stroke Impact Scale 3.0 (c)	ANCOVA
g) Goal attainment	MLWP > BWSTT	Patient Specific Function Scale(c)	ANCOVA
h) Walking participation	MLWP < BWSTT	Mean daily step activity	ANCOVA
i) Training staff requirement	MLWP < BWSTT	Total number of trainers/number of training sessions (c)	T-test
j) Meaningful change in gait speed of ≥ 0.14 m/s	MLWP > BWSTT	Comfortable gait speed change score T2-T1 ≥ 0.14 m/s)(b)	Chi-square test
Adverse events (count)			
a) Falls during session		Therapist report (b)	Chi-square test
b) Injury during session		Therapist report (b)	Chi-square test
c) Falls between session		Patient report (b)	Chi-square test
d) Myocardial Infarction		Patient report/health record (b)	Chi-square test
e) New stroke		Patient report/health record (b)	Chi-square test
f) Hospitalization		Patient report/health record (b)	Chi-square test
g) Death (all causes)		Health record/Physician (b)	Chi-square test

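### The text tests adverse events only where a difference already looks notable, by no stated criterion, while Table 3 tests all seven, so the data can decide which safety p-values appear

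*Protocol article*

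**What the plan says.** Two places in the protocol article govern the comparison of adverse events.

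- **Secondary Analysis (text).** Presentation comes first: "Descriptive statistics (i.e. means, or frequencies) will be used to present data related to adverse and serious adverse events by groups". Testing is then conditional: "Any apparently significant differences between groups will be analysed for significance using chi square statistics". No threshold, chart rule or responsible person is given for deciding that a difference qualifies.
- **Table 3.** The Sensitivity Analyses section introduces it with "Refer to Table 3 for a summary of the planned analyses". Its adverse-event block has seven rows: falls during sessions, injury during sessions, falls between sessions, myocardial infarction, new stroke, hospitalization and death. The method column reads "Chi-square test" in every row, with no condition.

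The general Statistical Analysis section adds "All statistical tests will be performed using two-sided tests at the 0.05 level of significance". The article gives no expected rate for any adverse event, does not say whether the chi-square is continuity-corrected, and names no method for small counts.

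**The concern.** A rule that looks at the table first and tests only what stands out lets the result decide whether it is tested. The p-values that reach the report are then a selected set, and a reader who takes each at face value misreads it. Because the criterion is undefined, two analysts could test different rows from the same data. Because Table 3 gives a different rule, either choice could be defended afterwards as planned.

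Events that do not pass the screen are promised frequencies only. With 35 per arm, a row that looks unremarkable is still compatible with a material difference, and only an interval shows that. Safety is a real comparative question here, since one arm practises varied tasks overground, partly outdoors and with little physical guidance, while the other walks in a harness on a treadmill.

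A secondary question is whether an unspecified chi-square test is stable enough for the rows likely to have few events.

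**Working it through.** **Inputs.** Seventy participants allocated 1:1 (Sample size; Randomization), so 35 per arm; two-sided alpha of 0.05 (Statistical Analysis). Event rates are not in the document. Those below are assumptions, shown as a range.

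**The plan's own figure.** n per arm = 2 × (1.960 + 0.842)² × 0.19² / 0.14² = 28.9, so 29. Allowing for 17% loss, 29 / 0.83 = 34.9, so 35 per arm and 70 in total. This reproduces.

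**Step 1: the two rules side by side.** Under the text, between none and seven events are tested, depending on the data. Under Table 3, seven are tested. The rules agree only if all seven differences happen to pass the screen. This step needs no assumption about rates.

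**Step 2: what the screen does to error.** As an illustration, let the screen be an uncorrected chi-square p<0.20 (an assumption; the article gives no criterion). All 35 v 35 tables were enumerated under equal true rates.

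| Event rate in both arms | Chance of p<0.05, no screen | Chance of p<0.05, with screen | Share of tests run that give p<0.05 |
|---|---|---|---|
| 1% | 0.06% | 0.06% | 0.9% |
| 2% | 0.5% | 0.5% | 3.3% |
| 5% | 3.6% | 3.6% | 15% |
| 10% | 5.7% | 5.7% | 27% |
| 20% | 4.9% | 4.9% | 25% |

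The second and third columns agree because every table with p<0.05 also has p<0.20. The screen therefore adds no false positives for a given event. It changes the denominator: among tests actually run and reported, the share reaching p<0.05 under no true difference rises well above 5% from an event rate of about 5%. At 1% to 2% it does not.

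**Step 3: how few events count as sparse.** With equal arms, the expected count in each event cell is half the total number of participants affected. An expected count of 5 needs 10 of 70 (14%). The probability of fewer than 10 is 0.998 at a 5% rate, 0.84 at 10% and 0.085 at 20%.

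**Step 4: sensitivity to the form of test.** Take 0 v 4 events, 35 per arm, so an expected count of 2 in each event cell.

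- Uncorrected: 70 × (4×35 − 0×31)² / (35×35×4×66) = 1,372,000 / 323,400 = 4.24, p=0.039.
- Yates: 70 × (140 − 35)² / 323,400 = 2.39, p=0.122.
- Fisher: 2 × C(35,4) / C(70,4) = 2 × 52,360 / 916,895 = 0.114.

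For 0 v 5 the p-values are 0.020, 0.063 and 0.054. At 0 v 6 all three fall below 0.05 (0.010, 0.033, 0.025).

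**Step 5: what frequencies alone leave open.** For an arm with 0 of 35 affected, the exact two-sided 95% upper limit is 1 − 0.025^(1/35) = 0.100, or 10%.

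**The case against.** The strongest reply has five parts.

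1. **The screen creates no false harm signals.** This is right (Step 2). A reader might infer that the safety comparison becomes much more likely to declare a spurious difference, or that a quarter of null tests will come out positive. The document supports neither. The first confuses the error rate per event with the share among tests run. The second holds only under an assumed screen at p<0.20 and event rates of roughly 10% or more.

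2. **Chi-square is not broadly unreliable at this size.** This is also right. Its unselected size stays at or below about 6% at every rate checked, and it under-rejects for truly rare events. A reader might point to 2 v 8 (0.040 against 0.084 by Fisher) as a sparse-cell failure, but its expected counts are exactly 5, so that gap reflects Fisher's conservatism. Fisher's size is 0.26% at a 5% rate and 1.3% at 10%, so replacing chi-square in every row would cost sensitivity to harm. What stands is narrower: in single sparse tables, the unstated form of the test decides which side of 0.05 the result falls.

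3. **Table 3 is only a summary.** It could be read as naming the test, with the text supplying the condition. That reading is possible, but nothing in Table 3 signals a condition, and the condition itself has no criterion. The passages still need reconciling.

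4. **All events are described by group, so readers can derive intervals.** This partly stands, because the descriptive presentation is not screened. General statements also promise 95% intervals, for models in the Statistical Analysis section and for all analyses in the remarks to Table 3. But for an event that is never analysed beyond description, the text promises frequencies only.

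5. **A small-cell method is detail for an analysis plan.** Fair for the choice of exact test, which is why that is secondary here. The conditional rule and its conflict with Table 3 are statements the article makes, not omissions.

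**Conclusion.** The point holds as a defect in safety reporting. The text's rule is data-dependent and undefined, and it conflicts with the unconditional tests in Table 3. That part rests on the wording alone.

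Its size is moderate. The chance of a false p<0.05 for any one event is the same with or without the screen (5.7% at an assumed 10% rate, for example). The harm lies in interpretation: the reported p-values lose their nominal meaning, chiefly for commoner events such as falls, and untested events may be left with no interval.

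The sensitivity of sparse tables to the form of test is a lesser point. It assumes that myocardial infarction, new stroke and death will be rare, which is reasonable over a programme of five to seven weeks and eight weeks of follow-up but is not stated. Falls, and perhaps hospitalization, may be common enough for chi-square. Neither the primary analysis nor the sample size is affected.

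**What to change.** 1. Delete the sentence in Secondary Analysis that makes testing depend on how the difference looks, and state one rule in the same words there and in Table 3.
2. For each of the seven rows, whatever the observed difference, report the number and percentage of participants with the event per arm and the risk difference with an exact or score-based 95% confidence interval.
3. If p-values are kept, give them for all seven rows. Name the form of the chi-square test (corrected or not) and a small-sample method for tables with expected counts below 5.

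The cost is wording only, with no new data and no change to design or sample size. The downside is that exact tests are less sensitive: among tables with no events in one arm, the smallest split reaching 0.05 moves from 4 v 0 with the uncorrected chi-square to 6 v 0 with Fisher. Limiting the small-sample method to sparse rows contains that loss, and the interval keeps a possible harm visible either way.

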#### Increasing Complexity of Walking Task Practice

Using the concepts described by Gentile in her Taxonomy of Task Analysis [48] the training therapist will make each of the core tasks more complex through the addition of concurrent mental, verbal or physical tasks, adding a time restraint, altered terrain and/or lighting, increased duration, reduced predictability and/or performance of walking in a mobile environment.

The therapist will adjust the difficulty of practice tasks based on their assessment of the participant's ability to perform the task safely without maximum physical assistance.

Tasks will be practiced in a serial or random order, moving from task to task, avoiding repetition of one station more than two times in a row. Feedback will be delayed and participants will be asked to self-evaluate their performance on a task and develop strategies to improve performance. When feedback is given, it will include either knowledge of results (e.g. time taken to complete a specific task) or knowledge of performance (e.g. step length, stance time) types of feedback [49]. The therapist will only provide hands-on guidance or assistance when required for safety, or for initial completion of the basic task. Specific handling or facilitation techniques will not be used to affect quality of gait. Participants will practice walking tasks with and without their preferred gait aid. Tasks will be practiced in the physiotherapy gym and/or more natural settings inside and outside the hospital (e.g. courtyard, sidewalks, hospital lobby). The tasks will be designed to encourage inclusion of both lower limbs during practice (e.g. reciprocal stepping up stairs). Each session will last 45 minutes including intermittent rest periods as required. Participants will practice three times a week for five weeks for fifteen sessions. Refer to Figure 2 for a graphic representation of the Motor Learning Walking Program.

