### Comparison Intervention: Body Weight Supported Treadmill Training (BWSTT)

Participants in the control group will practice walking on a treadmill according to a protocol based on an intervention described by Sullivan et al. [33] and Duncan et al. [50]. Based in the CPG theory of stepping control and recovery [51], the focus of this intervention is to provide participants with an opportunity to practice many repetitions of the normal gait cycle. Within a 45-minute session, participants will practice walking for up to 30 minutes at a time on the treadmill. Participants will train using the LiteGait system (harness and mechanical overhead suspension) and the GaitKeeper treadmill (Mobility Research Inc.). All participants will initiate training with 30% of their total body weight supported. A maximum of 40% body weight support will be provided during training. As recommended in the literature [33,52], participants will practice walking on the treadmill at speeds above their preferred overground walking speeds, preferably at or above 0.89 m/s (or 2.0 mph). Physical guidance will be provided by 1 to 3 therapists at the participant's pelvis, and/or their limbs to increase gait symmetry, facilitate weight shift, increase hip extension during stance, and to correct foot placement. Verbal feedback related to the participants gait pattern (knowledge of performance) will be provided frequently and concurrent to participants walking on the treadmill. Continuous visual feedback will also be provided via a full-length mirror. Participants will be discouraged from placing their hands on the LiteGait or treadmill handles during training. Body weight support, feedback, and guidance will be weaned, and treadmill speed adjusted according to a clinical decision making algorithm modified from a training algorithm described for individuals with spinal cord injury by Behrman et al. [53]. A comparison of key elements of the MLWP and BWSTT are provided in Table 1.

**Table 1 T1:** Description of experimental and comparison interventions

Learning Variable/Principle	Motor Learning Walking Program	Body Weight Supported Treadmill Training
**Amount of Practice/Intensity**	Up to 40 minutes of walking activity per session 15 sessions over 5 weeks	Up to 30 minutes treadmill walking per session 15 sessions over 5 weeks
**Specificity Of Practice**	Reflects task and environmental demands of community walking	High repetitions of near normal gait cycle on treadmill

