For experimental and control interventions, blood pressure (BP), heart rate (HR) and rating of perceived exertion (RPE) will be measured at the beginning, during rest periods and at the end of every treatment session. During training, exercise intensity will be reduced if HR exceeds 70% of age predicted maximal heart rate (220 - age) or RPE is greater than 13 on the Borg RPE scale. If resting BP exceeds 180 mmHg systolic and/or 100 mmHg diastolic, the exercise session will be stopped and their physician notified. This information will be recorded allowing comparison between groups. Patients will also wear the StepWatch 3^© ^step activity monitor during training sessions, and mean number of steps taken during the sessions recorded as a measure of amount of task-related practice.

In the event of missed sessions, participants will be allowed a maximum of seven consecutive weeks to complete as many of the fifteen sessions as possible. Considering that previous studies have demonstrated changes in walking skill following 12 [24,25,33,34] and 18 sessions [19] over 4 [24,25,33,35] to 6 [19,34] weeks, we expect that a training frequency of 2 to 3 sessions per week for a total of 15 sessions will be result in improved walking skill in our participants.

To minimize the risk of contamination, separate training physiotherapists will deliver the Motor Learning Walking Program and the BWSTT program. All therapists will undergo a standardized training program prior to treating study participants on their own. The principal investigator will monitor ongoing competence and adherence through session observation, case discussions and documentation reviews. In order to minimize the impact of expectation bias, training therapists and participants will be blinded to the hypotheses of the investigators regarding which of the two interventions is expected to result in superior outcomes. To avoid co-intervention, participants will be asked to refrain from attending physiotherapy for their balance or walking limitations during the study intervention period. Participants will be questioned at post-intervention and follow up measures regarding their participation in physiotherapy outside of the study.

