## Discussion

To date, a number of controlled trials have tested the effectiveness of intensive, task-related walking training interventions against a non-walking focused control treatment.

A head-to-head comparison of two different active walking focused interventions will help answer the question whether it matters *how *individuals practice walking after stroke. As with most rehabilitation interventions, task-related walking training can be complex and multifaceted. A sound theory base can help focus an intervention on the proposed, relevant active ingredients [74]. In our study, the experimental and comparison intervention were designed based on two different theoretic frameworks. While both interventions emphasize walking practice, their respective theory bases dictate what type of walking is practiced, the practice environment, tolerance for error and variability during practice, the role of the therapist, and the role of the participant during practice. As a result, this study provides a direct comparison of the effectiveness of two quite different task-related walking training protocols with different resource requirements. The results of this study takes an important step toward informing clinicians, patients, caregivers and administrators of the essential components of an optimally effective task-related walking training intervention following stroke.

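### One section has patients in both arms wear the step monitor in training; another counts steps only in a convenience sub-sample, so delivered practice may not be described in the randomised groups

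*Protocol article*

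**What the plan says.** **Who has steps counted.** The paragraphs after Table 1, in the section on the comparison intervention, cover both interventions. They say that patients will wear a "step activity monitor during training sessions, and mean number of steps taken during the sessions recorded as a measure of amount of task-related practice". No sub-group is mentioned.

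The Secondary Analysis section says that "the mean number of steps taken per session will be counted in a convenient sub-sample of participants using the step activity monitors". It gives the purpose as describing the two interventions, and it compares the groups with an independent-samples t-test. It states neither the size of the sub-sample nor how participants or sessions enter it.

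**How much practice is allowed.** Under amount of practice, Table 1 gives "Up to 40 minutes of walking activity per session 15 sessions over 5 weeks" for MLWP and "Up to 30 minutes treadmill walking per session 15 sessions over 5 weeks" for BWSTT. The text above the table words the BWSTT limit differently: within a 45-minute session, "participants will practice walking for up to 30 minutes at a time on the treadmill". The MLWP text also sets a 45-minute session: "Each session will last 45 minutes including intermittent rest periods as required".

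**What the trial is meant to inform.** The Discussion says that the comparison will help to show whether it matters how "individuals practice walking after stroke".

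**The concern.** The two statements on steps describe different data sets. Under the first, the comparison can be made between the arms as randomised. Under the second, it is made between people chosen for convenience, and randomisation does not protect that contrast.

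This bears on interpretation. Steps per session is the only measure that the protocol labels as amount of practice. The guiding statements for MLWP themselves link more repetitions to more learning. With different time ceilings in Table 1, a reader of the results will ask how much walking each arm actually did. If the answer comes from a small, convenience-chosen group, it could mislead either way. A difference could be produced by selection, and a non-significant test could be taken as evidence of equal practice.

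**Working it through.** **1. The plan's own figure.** No design figure is given for session steps. The only calculation is for gait speed, in Sample size: a difference of 0.14 m/s, SD 0.19 m/s, two-sided 0.05, 80% power.

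- n per arm = 2(1.960 + 0.842)² × 0.19² / 0.14² = 28.9, so 29.
- With 17% loss: 29 / 0.83 = 34.9, so 35 per arm and 70 in total.

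Both figures reproduce and are not in dispute. They serve here only to fix 35 as the largest planned number per arm.

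**2. The ceilings.**

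- MLWP: 15 × 40 = 600 minutes at most. If the 15 minutes of goal setting fall inside the first 45-minute session, 14 × 40 + 30 = 590.
- BWSTT, by Table 1: 15 × 30 = 450 minutes at most.
- Ratio 600/450 = 1.33, or 590/450 = 1.31.
- BWSTT, by the text: if 30 minutes limits a single bout, only the 45-minute session bounds the total. The ratio of per-session limits could then fall towards 40/45 = 0.89, an outer bound that ignores rest.

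So the stated minutes do not settle which arm is allowed more walking, still less which arm does more.

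**3. What convenience selection does to the t-test.** Within an arm, let the shift be mean steps among selected participants minus mean steps among everyone randomised to that arm. Then:

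expected sub-sample difference = difference between randomised arms + (MLWP shift − BWSTT shift)

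A selection rule that is the same in both arms and unrelated to walking, such as random choice within arm, makes both shifts zero on average. Convenience selection does not ensure this. Different therapists deliver the two programmes, so the shifts could plausibly differ. The documents give no basis for the size or sign of the bias.

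**4. Precision.** The sub-sample size is not given, so a range is assumed. The 95% CI half-width in SD units is t(0.975; 2m − 2) × √(2/m) for m per arm. For m = 10 this is 2.101 × 0.447 = 0.940, and for m = 35 it is 1.995 × 0.239 = 0.477.

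| Per arm (assumed below 35) | CI half-width (SD) | Width relative to 35 per arm | Difference detectable with 80% power (SD) |
|---|---|---|---|
| 35 | 0.477 | 1.00 | 0.68 |
| 20 | 0.640 | 1.34 | 0.91 |
| 15 | 0.748 | 1.57 | 1.06 |
| 10 | 0.940 | 1.97 | 1.33 |
| 5 | 1.458 | 3.06 | 2.02 |

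**5. An illustration.** Suppose that one arm takes 33% more steps (the 40:30 ratio at equal cadence, an assumption).

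- Coefficient of variation 0.5 (assumed): the t-test has about 79% power with 35 per arm, 42% with 15, 29% with 10 and 15% with 5.
- Coefficient of variation 0.3 (assumed): above 99%, 84%, 65% and 34%.

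A small sub-sample could therefore miss a difference as large as the ceilings allow, even without selection bias.

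**The case against.** The strongest reply is that the two statements may not conflict. The intervention text sets blood pressure, heart rate and exertion for every session, but for the monitor it says neither every session nor every patient. The Secondary Analysis section could simply be filling in the detail. Session steps are also a process measure: they are missing from the listed outcomes and from Table 3, and their stated purpose is descriptive. Heart rate and perceived exertion are recorded in both arms at each session.

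Part of this stands. Recording in all patients is the natural reading of the intervention text, but not an explicit commitment. The descriptive purpose limits the consequence. Heart rate and exertion measure intensity rather than amount, so they fill the gap only partly. Even if the Secondary Analysis section is the intended version, it still plans a between-arm significance test on a convenience sample of unstated size.

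A reader might go further in three ways that the documents do not support.

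- **That practice dose differs by design, 40 against 30 minutes.** Both figures are upper limits, the sessions are equal in length and planned number, and the BWSTT limit is worded in two ways. BWSTT also aims at many gait-cycle repetitions, at speeds above the participant's preferred overground pace. MLWP time includes transitions, obstacles and picking up objects. More minutes need not mean more steps.
- **That amount of practice cannot be examined in the randomised arms.** This follows only if the Secondary Analysis wording governs.
- **That full step data would separate type of practice from amount.** Steps are measured after randomisation and belong to each treatment package. Complete data would describe delivered practice by arm without proving a mechanism.

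**Conclusion.** The inconsistency is real and should be corrected. If the Secondary Analysis section governs, the planned t-test is not a comparison of the randomised groups, and the trial may lack an unbiased description of delivered practice on the only measure that it labels as such.

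The size of any selection bias cannot be derived from the documents. The loss of precision depends on the unstated sub-sample size. It ranges from an interval 1.34 times as wide (20 per arm) to 3.06 times as wide (5 per arm), relative to 35 with data. These sizes are assumptions.

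The consequence is confined to interpretation. The primary comparison of post-intervention gait speed remains valid, and the listed outcomes are untouched.

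**What to change.** 1. Reconcile the two statements by removing the convenience selection from Secondary Analysis. Suggested text:

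> Steps will be recorded in all randomised participants at every training session (or at sessions fixed in advance, for example 3, 8 and 13). Mean steps per session will be reported by randomised arm, with the difference and its 95% CI, as a descriptive process measure beside the primary result. The number of participants and sessions contributing will be given for each arm.

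2. If a sub-sample must be kept, choose participants and sessions by a pre-set rule that is the same in both arms, for example at random within arm. State its size and label the comparison descriptive.

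3. Reconcile the two wordings of the BWSTT 30-minute limit in the text and Table 1, so that the ceilings can be compared. Which wording is meant is for the investigators to say.

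The cost is monitor use and data handling at the chosen sessions. The same type of monitor is already planned at all three assessments for daily step activity, so the added burden should be small. The documents do not say how many monitors are available. If supply is the constraint, fixed sessions are the cheaper form.
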